##### ED visits

Number of ED visits over the past year will be extracted from medical records at baseline and at 12-months. Furthermore, ED visits over the past 6 months will be assessed at baseline, 6- and 12 months. ED visits at baseline will serve as covariate in the analyses, whereas the remaining measures will serve as outcome in the mains analyses.

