### Participants

Patients visiting the ED implementing the CM intervention are eligible if they are ≥18 years, able to communicate in a language that is spoken by the local team or a professional interpreter and have ≥5 ED visits in the past 12 months recorded. Exclusion criteria include presenting less than 2 vulnerability dimensions (i.e., social, somatic, mental, risk behaviors) besides frequent ED use, being unable to give informed consent, planning to stay in Switzerland less than 18 months, not expected to survive at least 18 months, awaiting for incarceration or being currently incarcerated, having a family member already enrolled in the study.

Given that this research study aims to disseminate and implement a CM intervention, we are neither aware of the number of hospitals that will eventually participate, nor of the number of participants who will be enrolled in each hospital.

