### The CM intervention

The CM intervention, as developed by our research team, typically includes the following steps. First, health-care providers and/or administrative staff detect FUEDs in the ED through an electronic alert in patients’ files. They then notify the case manager that a FUED is in the ED. Next, if the FUED visiting the ED agrees to do so, the case manager makes a first evaluation of the FUED’s situation in the ED, aiming to identify his main problems, the involved health-care network and the priorities that need to be addressed. After this first contact and if the FUED agrees ambulatory care, the case manager writes an intervention report and sets an appointment with the patient. Notably, case managers send on a case-by-case basis letters summing up their intervention to FUEDs’ general practitioner or other involved physicians. Ambulatory care consists of setting a number of appointments with the case manager on a case-by-case basis (in the ED, in the community or health-care network, or at the patient’s home depending on situation and needs). Concretely, the case manager, together with the patient, identifies objectives based on the patient’s specific needs, which will define the total number of appointments needed. Ambulatory care aims at reaching these objectives through appointments with the involved health-care network and referral to specialized services fitting the patient’s needs. Staff involved in this step include the case manager, specialized workers from the health-care network, and sometimes, the patient’s relatives. Whenever possible, the patient is asked to be active in the decisions taken to address his social and medical needs (patient empowerment). The intervention concludes when the patient is integrated into a coordinated and functional health-care network.

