#### The operation phase

The CM intervention will be implemented at all sites included in the study. First, case managers will conduct a screening process to identify eligible participants. At each site, patients fulfilling the inclusion criteria will be contacted by the case managers. The number of participants included will depend upon each site resources. We expect that each site will include at least 2 participants per week on average. The maximum number of inclusions per week per site will be discussed with the research nurse (from I-CaM staff) in charge of the clinical training and supervision in order to avoid inducing work overload. If possible (depending upon resources on each site), eligible patients having been treated in the ED in the 10 days prior the recruitment window will be contacted by phone and proposed to come back to the ED to participate in the study. Remaining FUEDs (i.e., the FUEDs not invited to participate in the study) will receive usual care.

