When first meeting the participant, the case managers will present the study and examine the exclusion criterion. If the patient does not have any exclusion criteria and is interested in participating, the case managers will conduct the informed consent process. After providing written consent, participants will receive the CM intervention. After each inclusion on site, the case managers will up-date the I-CaM research team in charge of the clinical assessment (i.e., baseline and follow-up assessments of the health-related variables to describe participants’ trajectories). The I-CaM research team will contact participants and conduct the baseline assessment within 10 days following the inclusion. Participants will then complete follow-up assessments at 3, 6 and 12 months post-baseline. All assessment interviews will be conducted by phone by bachelor-level students (i.e., of medical or social sciences) who will be trained and weekly supervised. For all patients, incentives (i.e., gift cards of 10, 20 and 20 CHF for the 3, 6 and 12-month follow-ups, respectively) and reminders will be used to compensate participation and obtain good retention rates. Other clinical variables (see measures section) will be directly extracted from medical records on-site by the I-CaM research team. Each site implementing the CM intervention will monitor their activities (e.g., tracking the number of eligible patients and the number who received the CM intervention). At the end of the operation phase, the research team will conduct semi–structured interviews with case managers and champions. Both champions and case managers will also complete a questionnaire.

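### Every baseline ED-visit window contains a guaranteed index visit that no follow-up window has, so a pre-post comparison shows a fall in ED use even without any effect

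*Protocol article*

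**What the plan says.** **Recruitment.** Participants requires that patients visiting the ED "have ≥5 ED visits in the past 12 months recorded". The CM intervention says that staff "detect FUEDs in the ED through an electronic alert in patients’ files". The operation phase adds an optional route, depending on site resources: eligible patients treated in the ED in the preceding 10 days "will be contacted by phone and proposed to come back to the ED to participate in the study".

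**Timing.** The operation phase states: "After providing written consent, participants will receive the CM intervention". The research team is then to "conduct the baseline assessment within 10 days following the inclusion", and follow-ups are timed from baseline.

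**Counts.** ED visits states: "Number of ED visits over the past year will be extracted from medical records at baseline and at 12-months". Visits over the past 6 months are read at baseline, 6 and 12 months. The section makes the baseline count a covariate and the later counts the outcome. Table 3, however, lists ED visits among the clinical outcomes at baseline, 6 and 12 months. Design describes a within-subject pre-post comparison, and Aims of the study expects ED visits to decrease after the intervention. Clinical measures names ED use as a main outcome.

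**Place of appointments.** The CM intervention allows case-manager appointments "in the ED, in the community or health-care network, or at the patient’s home depending on situation and needs".

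**The concern.** Recruitment is conditional on an event of the same kind as the outcome. The index visit necessarily precedes baseline, so it lies in both the past-year and the past-6-months windows read there. Nothing guarantees a visit in any follow-up window. The article does fix the windows and the recruitment route, and it gives no rule that removes the index visit. Taken as written, a before-after comparison of ED visits is tilted towards the decrease that the study expects, and there is no control group to show how much of the fall is artefact.

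Three smaller gaps bear on the same counts:

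- A call-back attendance, if registered as an ED visit, also falls before baseline and enlarges the pre count.
- A case-manager appointment held in the ED, if registered, enlarges the follow-up count. How often this happens could differ between sites.
- The intervention can start before the baseline assessment, so up to 10 days of treated time can lie in the pre window.

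**Working it through.** **The document's own effect figure.** Case management intervention effectiveness gives 2.71 versus 3.35 visits over 12 months. 2.71/3.35 = 0.809, which reproduces the stated 0.81 (a 19% relative reduction). The difference is 3.35 − 2.71 = 0.64 visits. This is a contrast between arms, so it serves here only as a yardstick of size.

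**Index visit counted only before baseline, no true change.** Let n be the 12-month pre count including the index visit. The underlying yearly number is then n − 1.

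- 12-month ratio, post/pre = (n − 1)/n.
- 6-month pre count = 1 + (n − 1)/2; post count = (n − 1)/2; the ratio is post/pre.

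| n | 12-month ratio | 6-month pre | 6-month ratio |
|---|---|---|---|
| 5 | 4/5 = 0.80 | 3.0 | 2.0/3.0 = 0.67 |
| 6 | 5/6 = 0.83 | 3.5 | 2.5/3.5 = 0.71 |
| 8 | 7/8 = 0.875 | 4.5 | 3.5/4.5 = 0.78 |
| 10 | 9/10 = 0.90 | 5.5 | 4.5/5.5 = 0.82 |

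The smallest n is 5 because that is the eligibility threshold. The article gives no expected visit rate, so the range up to 10 is an assumption.

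**Separating this from regression to the mean.** In a simulation, each patient had a constant visit rate. Rates varied between patients by a gamma distribution, with assumed means of 1, 2 and 3 visits a year and shapes of 0.3, 0.5 and 1.0 respectively. Patients were recruited at a visit, at least 5 visits were required (with the index visit either counting or not counting towards the 5), and the intervention had no effect.

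| Window | Ratio, index counted | Ratio, index excluded |
|---|---|---|
| 12 months | 0.79 to 0.84 | 0.89 to 0.93 |
| 6 months | 0.72 to 0.77 | 0.89 to 0.93 |

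One example: with mean 2, shape 0.5 and the index counting towards the 5, the mean pre count is 9.03 without and 10.03 with the index visit, and the mean post count is 8.42. The ratios are 8.42/9.03 = 0.93 and 8.42/10.03 = 0.84. Compared scenario by scenario, excluding the index visit removes about 8 to 10 percentage points of false reduction over 12 months and 15 to 18 over 6 months. The remaining 7 to 11 points are regression to the mean.

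**Call-back attendance, if registered.** It adds one more visit to the pre count, so the 12-month ratio becomes (n − 1)/(n + 1): 4/6 = 0.67 at n = 5 and 9/11 = 0.82 at n = 10.

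**Case-manager appointments in the ED, if registered.** On the earlier trial's scale, an average of 0.64 per patient-year would cancel the whole difference (2.71 + 0.64 = 3.35). An average of 1 would give 3.71/3.35 = 1.11. These figures are illustrative only.

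**Treated days in the pre window.** At most 10/365 = 2.7% of the 12-month window or 10/182 = 5.5% of the 6-month window.

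**The case against.** The strongest reply is that ED visits makes the baseline count a covariate and only the later counts the outcome. One extra visit in everyone's covariate shifts the intercept if it enters linearly, and leaves the contrast between 6 and 12 months essentially untouched. That is right, and on this reading the index-visit bias largely drops out. But so does the pre-post comparison. The past-year count would have a single outcome value, at 12 months, and the 6-month count would give only 6 versus 12 months. Neither estimates the decrease expected in Aims of the study.

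A second reply is that Limitations already concedes regression to the mean and promises caution. It does not mention the index visit, which is a separate component and, unlike regression to the mean, can be removed by definition.

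A third is that an article may leave extraction rules to the full protocol. That is fair for the registration of call-back and case-manager attendances. It is less so for the index visit, because the article itself fixes the windows and the recruitment route that create the imbalance.

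A reader might go further and infer three things that the document does not support:

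- That the study creates the index visit. It is a genuine visit; the problem is selection at an event.
- That call-back attendances inflate follow-up. The patient returns in order to be included, and baseline comes afterwards.
- That case-manager appointments are counted as ED visits. No text says so, and Health-care re-orientation refers to separate records of the CM intervention.

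**Conclusion.** The point holds for any comparison of baseline with follow-up ED visits. With no true change, the index visit alone gives a false fall of 20% (5 visits including the index) to 10% (10 visits) over 12 months, and of 33% to 18% over 6 months. This is comparable with the effect in the team's randomised trial, which was itself not significant.

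The result assumes a constant visit rate in each patient and follow-up windows that start after the index visit. The split between index visit and regression to the mean rests on assumed visit rates. If call-back or case-manager attendances are registered as well, the former exaggerate the fall and the latter mask it, so the net direction of all the effects together cannot be known from the article. The effect of treated days in the pre window is minor.

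**What to change.** 1. Anchor every ED-visit window on the inclusion date rather than the baseline interview. End the pre windows before the index visit, start the post windows on the day after inclusion, and keep their lengths equal.
2. Exclude the index visit, attendances made only to enrol, and case-manager appointments from all ED-visit counts. The eligibility count need not change.
3. Reconcile the covariate wording under ED visits with the pre-post aim. State whether the baseline count is part of the outcome or only an adjustment variable, and which contrast estimates the decrease.
4. Report a sensitivity analysis with the index visit included.

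The cost is a little more extraction work. It requires visit dates, and a way to tell case-manager or enrolment attendances from visits for care; the article does not say whether the records hold the latter. Excluding the index visit will make the apparent reduction smaller. Regression to the mean remains and still calls for the caution promised in Limitations.

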### Aims of the study

To the best of the authors’ knowledge, no previous study has focused on the implementation of a CM intervention for FUEDs in Switzerland. French-speaking Switzerland includes 7 cantons and covers 23% of the extension of the country (with 2 million persons in 2015). ED overuse is of practical concern to public health advisors and clinicians. Research focusing on both implementation and clinical outcomes may provide key insights into the mechanisms and processes for disseminating and implementing a CM intervention for FUEDs into broader practice in the real-world settings. This study aims at 1) implementing a CM intervention for FUEDs in public hospitals with EDs in the French-speaking region of Switzerland, 2) studying the process of implementation of the intervention and, 3) studying CM intervention’s effectiveness among FUEDs. Regarding the intervention effectiveness assessment, we expect that FUEDs will evince improvements in clinical outcomes (e.g., higher scores in quality of life) and decreases in ED visits after receiving the CM intervention.

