## Methods and design

### Design

This research project features a Type 2-hybrid study design focusing on both implementation and clinical outcomes [27]. The implementation part of the study uses mixed methods a) to describe both qualitatively and quantitatively factors that may influence implementation process and b) to assess implementation outcomes. The clinical part of the study uses a within-subject design (pre-post intervention) to evaluate participants’ trajectories after receiving the CM intervention.

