ED visits	Extracted from medical records	Baseline, 6, and 12 months
Health-care reorientation	Extracted from medical records	Baseline, 3, 6, and 12 months
Quality of life	WHOQOL-BREF	Baseline, 3, 6, and 12 months
Empowerment	Health Care Empowerment Inventory	Baseline, 3, 6, and 12 months
Self-efficacy	Self-Efficacy Scale	Baseline, 3, 6 and 12 months
Health literacy	European Health Literacy Project Questionnaire	Baseline, 3, 6 and 12 months
Problematic alcohol use	AUDIT-C	Baseline, 3, 6 and 12 months
Precursors of alcohol use	Visual analog rulers assessing importance, intentions, readiness and confidence regarding alcohol use changes	Baseline, 3, 6 and 12 months

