##### Health-care re-orientation

Health-care re-orientation will be extracted from the CM intervention medical records at 12 months. Health-care reorientation at 12 months will be used as outcome.

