#### Clinical outcomes

Data will be screened for missing cases, outliers, and normality of distributions using descriptive statistics and plots. We will take appropriate steps to deal with missing data. First, we will conduct analyses to detect missingness patterns and test whether they may be considered “ignorable.” [48] If more than 5% of outcome data are missing, [49] we will divide the sample into 2 groups (i.e., missing, not missing), and use fully observed variables to predict missingness on the affected outcome. If fully observed variables are not significant predictors, missingness may be considered as “observed at random” and fulfilling some criteria for “missing completely at random” (MCAR) assumptions. In that case, we will use multiple imputations procedures for measured outcomes and direct maximum likelihood estimation for structural models. If data missingness is non ignorable (MNAR), we will use pattern-mixture models with multiple imputation to model the missingness mechanism.

Main analyses will comprise multilevel models (i.e., MLM; mixed effects model) [50] utilizing appropriate distributions for the outcome variables (e.g., Poisson, negative binomial, normal). MLM examine the effect of time (after receiving the CM intervention) on clinical outcomes (e.g., quality of life, self-efficacy). MLM is appropriate to handle nonindependence data. Specifically, data will be clustered by participants (i.e., repeated measures) and by hospitals. MLM does not assume independence of observations. Dependence is modeled through random effects (representing different sources of variability in the data). We will include sources of random variability at the group level accounting for between-group differences and another random effects for the individual accounting for within-person differences in the repeated measures. MLM will be adjusted for demographic variables (i.e., age and gender), ED use, at-risk behaviors (e.g., alcohol use disorders) and health status. Descriptive statistics will be conducted on SPSS and MLM on STATA. The significance level will be set at *p* = .05.

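### Baseline ED visits are made a covariate, not an outcome, so read literally the single-group model gives no before-versus-after contrast for a main outcome

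*Protocol article*

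**What the plan says.** Aims of the study expects "decreases in ED visits after receiving the CM intervention". The Design section sets out how this is to be shown: "The clinical part of the study uses a within-subject design (pre-post intervention"), with no comparison group. Clinical measures names ED use as one of the two main outcomes.

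The ED visits section defines two counts:

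- Past-year count: "Number of ED visits over the past year will be extracted from medical records at baseline and at 12-months".
- Six-month count: "ED visits over the past 6 months will be assessed at baseline, 6- and 12 months".

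It then assigns their roles: "ED visits at baseline will serve as covariate in the analyses, whereas the remaining measures will serve as outcome in the mains analyses".

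The data analysis plan for clinical outcomes names the effect to be tested: "MLM examine the effect of time (after receiving the CM intervention) on clinical outcomes". Its single adjustment list, for all outcomes, includes ED use.

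Table 3 has a separate block for descriptive variables and covariates. ED visits are not in it. They stand under clinical outcomes, timed at baseline, 6 and 12 months.

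On a separate matter, the section on health-care re-orientation says "Health-care reorientation at 12 months will be used as outcome", while Table 3 times the same variable at "Baseline, 3, 6, and 12 months".

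**The concern.** Adjusting for the baseline value while modelling only follow-up values is sound in a two-arm trial, because the contrast of interest is between arms. Here there is no arm. The only contrast the model can offer is time, and a time effect that is to show a fall after CM needs the pre-inclusion count among the outcomes. The sentence on roles takes it out.

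A team following that sentence could report no change over time after a real fall. It could also report a significant decrease when visits rose in the first six months and merely returned to their starting level. Either way, the stated hypothesis on a main outcome would not have been tested.

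**Working it through.** The article gives no sample size, power or expected count for the clinical part, so there is no figure to reproduce. The check is on the structure of the model.

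**1. Outcome rows left by the stated roles**

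| Count | Measured at | Covariate | Outcome rows | Time effect available |
|---|---|---|---|---|
| Past year | baseline, 12 months | baseline | 1 (12 months) | none |
| Six months | baseline, 6, 12 months | baseline | 2 (6 and 12 months) | months 6–12 vs 0–6 |

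**2. What the six-month time effect estimates.** Write log E(Y) = a + b·t + g·log(1 + baseline) + u, with t = 0 at 6 months and t = 1 at 12 months, and u the participant effect. The baseline term is the same in both rows of a participant and cancels from the comparison. With complete data, exp(b) is the ratio of the two period totals. If a share p of the follow-up year's visits falls in the first half, exp(b) = (1 − p)/p:

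- p = 0.4: 0.6/0.4 = 1.50
- p = 0.5: 0.5/0.5 = 1.00
- p = 0.6: 0.4/0.6 = 0.67

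The pre-inclusion level does not appear.

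**3. Simulation.** All settings are assumptions: Poisson counts, gamma participant heterogeneity (shape 2), mean 4 visits per six months before inclusion, no hospital effect, no selection on baseline, 300 replicates, two-sided 0.05. Both models were fitted by Poisson GEE with robust standard errors, as a stand-in for the mixed model. The stated model has outcomes at 6 and 12 months with baseline as covariate. The repeated-outcome model has baseline, 6 and 12 months as outcomes with time as a factor, and its ratio is 12 months versus baseline. Each cell gives the mean ratio and the percentage of replicates with p < 0.05.

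| True course relative to baseline | Stated, n = 100 | Stated, n = 200 | Repeated, n = 100 | Repeated, n = 200 |
|---|---|---|---|---|
| No change | 1.00; 6% | 1.00; 6% | 1.00; 7% | 1.00; 5% |
| 0.81 in both halves | 1.00; 7% | 1.01; 4% | 0.81; 81% | 0.81; 98% |
| 0.50 in both halves | 1.00; 8% | 1.00; 8% | 0.50; 100% | 0.50; 100% |
| 1.50 in both halves | 1.00; 6% | 1.00; 4% | 1.50; 100% | 1.50; 100% |
| 1.25 at 6 months, 1.00 at 12 | 0.80; 93% | 0.80; 100% | 1.00; 5% | 1.00; 7% |

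The 0.81 is the between-arm ratio of the team's earlier randomised trial (Background), used only as an example size. The rejection rates depend on the assumptions. That the stated ratio does not depend on the pre-inclusion level does not.

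**4. How far a recovered post/pre ratio can be read.** In the earlier trial, visits over 12 months averaged 2.71 with CM and 3.35 in the control arm. Its pre-inclusion mean B is not given. I assume the same entry definition, so B is at least 5.

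- Post/pre at B = 5: CM 2.71/5 = 0.54; control 3.35/5 = 0.67.
- Control-arm fall as a share of the CM-arm fall, (B − 3.35)/(B − 2.71): at B = 5, 1.65/2.29 = 72%; at B = 6, 2.65/3.29 = 81%; at B = 8, 4.65/5.29 = 88%.

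Most of the before-after fall therefore also occurred without CM. As a second illustration, in a population with stable rates (gamma, assumed shape 1 and scale 1.5), people selected for five or more visits in a year fell from a mean of 6.5 to 4.5 with no intervention, a ratio of 4.5/6.5 = 0.69.

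**The case against.** The strongest reply is that the sentence on roles is loose wording in a condensed article. Table 3 lays out ED visits exactly as it does quality of life, as an outcome with a baseline, and the design is called pre-post more than once. On that view, baseline ED use is the covariate for the other outcomes' models, and the ED-visit model keeps its baseline row. This reading is possible, and it is why the point is a conflict to reconcile and not proof of what will be done. It is still the weaker reading: the sentence stands in the section on ED visits and splits those measures into a covariate and outcomes. If only the past-year baseline were the covariate and the six-month baseline stayed an outcome, that outcome row would be partly regressed on itself, because the past year contains the past six months.

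It can also be said that a baseline-covariate model yields a pre-post test once a contrast is added, such as log baseline as an offset, a change score, or the adjusted follow-up mean against the baseline mean. That is true, but none is stated; the stated test is time. Nor is this a detail left to a fuller plan, since the article assigns the roles itself.

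Finally, the Limitations section acknowledges regression to the mean and promises caution. That stands, and it governs how the repaired estimate should be read. It does not supply the missing contrast.

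**Conclusion.** The point holds for ED visits under the literal reading of the role sentence. The past-year count has no time effect, and the six-month count has one only between two periods after inclusion. The stated model therefore does not test the expected decrease in a main outcome, and the sentence conflicts with Table 3. The structural result needs no numerical assumption; the simulated rejection rates do.

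A reader might infer more than the documents support:

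- *That the study cannot assess change in ED use.* The baseline counts are collected, so the contrast is recoverable.
- *That quality of life and the scales share the fault.* Nothing removes their baselines from the outcome.
- *That the general adjustment list, or frequent ED use among the vulnerability determinants, repeats the error.* The list serves all outcomes and is reasonable for the others. Frequent ED use is only an example there, and as a yes/no entry criterion it would be constant.
- *That 0.54 is the effect being missed.* The control arm's 0.67 on the same assumed floor shows otherwise.
- *That robust standard errors deal with selection at five visits.* Only the past-year count has that floor, and they do not correct a selection-driven fall in the estimate.

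Health-care re-orientation is a separate timing mismatch. A reader might infer that its baseline value must be empty, but the article does not say when the CM record begins.

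**What to change.** 1. Reword the role sentence in the ED visits section so that pre-inclusion counts are outcome rows. Past-year count: the year before and the year after inclusion. Six-month count: the six months before inclusion, months 0–6 and months 6–12. Enter period as a categorical fixed effect and report the post/pre rate ratio with its confidence interval.
2. Drop baseline ED use as a covariate from the ED-visit model only; keep it for quality of life and the other outcomes. Say so beside the adjustment list.
3. State beside the estimate that entry at five or more past-year visits makes part of any fall regression to the mean, citing the earlier trial's two arms (3.35 and 2.71, both below 5). The ratio is descriptive and not a causal effect of CM.
4. Separately, reconcile the timing of health-care re-orientation between its own section and Table 3.

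The cost is a few sentences and, depending on how item 4 is settled, one table cell. Items 1 to 3 need no new data, because both counts are already extracted at baseline.
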